## Methods/design

### Study design

This is a multi-center randomized controlled trial. We will carry out the study in three large tertiary hospitals with anticoagulation clinics, three small tertiary hospitals and three county hospitals in Hunan province of China. Eligible patients will be randomly assigned to the SMART model group or the control group (usual care clinic and anticoagulation clinic). Patients in the SMART model group do PST at home once every two to 4 weeks. Control patients receive usual care without intervention. All the patients will be followed up through outpatient clinics, phone call or online interviews at the 3rd, 6th, 9th and 12th month. The percentage of time in therapeutic range (TTR), incidence of warfarin associated major bleeding and thromboembolic events and costs will be compared between the SMART model group and control groups. Figure 1 describes the study design.

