### Study participants and inclusion criteria

Patients eligible for this project have to comply with all of the requirements below: are expected to be on warfarin treatment for the duration of at least 12 months, accept the study protocol and randomization, and sign an informed consent. Patients who fall into any of the following criteria are excluded in this project, including pregnancy or plan to get pregnant in 18 months, had experienced a bleeding complication requiring treatment in the past 6 months, are unable to attend a hospital in 6 hours, renal failure (hemodialysis or glomerular filtration rate < 10 mL/min), dementia or unstable psychiatric conditions or receiving treatment for cancer.

A patient who has been enrolled in the project will be considered as a dropout if meets any of the following criteria and the reason will be recorded: the patient decides to withdraw for any reason; the patient in the SMART model group does not follow the health-care professionals’ instruction for at least twice; the researcher considers the patient is no longer physically and/or psychologically fit to remain in the study. The impact of dropouts on statistical analyses, including intention to treat, will be used by carrying the last observation forward.

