#### Follow-up visits and data collection

Each of the enrolled patients has to record his/her warfarin related information in a printed monitoring handbook, including INR results, warfarin dosage, other medicine, diet change, new disease, and thrombosis or bleeding events (if occurs). All the patients are required to receive follow-ups at the 3rd, 6th, 9th and 12th month through outpatient clinic visits, telephone or online interviews. At each follow-up time-point, the research stuff will collect the warfarin related information. Double data entry will be carried out to ensure data accuracy and data will be kept in encrypted mobile hard disks to protect patients’ privacy. Only the corresponding author has access to the final trial dataset. As shown in Table 3, patients are required to provide the information of warfarin dosage and INR results, the numbers of going to the outpatient clinics or inpatient treatment due to warfarin, quality of life as measured by the health index scale (EQ-5D-3L) [16], and the related treatment costs. At baseline and the last time visit, patients are required to fill in the Morisky anticoagulant compliance questionnaire [14] and the oral anticoagulation knowledge test [15]. An anticoagulation satisfaction survey by using the Duke Anticoagulation Satisfaction Scale [17] will be conducted to all the patients at the end of the study. The research staff will send text messages to remind the patients for follow-ups and all the participated patients will receive certain amount of compensation fees to sustain their involvement in the study.

**Table 3 Tab3:** Measurement domains, survey methods and collection time-points

Variable	Component	Measurement methods	Baseline	3rd M	6th M	9th M	12th M
**Socio-demographic parameters**	Gender, age, telephone, address, education, occupation and annual income	Face-to-face interview	√				
**Clinical parameters**	Height, weight, warfarin indication, start date of warfarin, warfarin dosage, TTR calculated by INR tests in the preceding 12 months, history of thrombosis or major bleeding, concomitant diseases and medicine Warfarin dosage, INR, bleeding or thrombosis, other clinical adverse events	Face-to-face interview	√				
		Face-to-face interview, telephone or online interview		√	√	√	√
**Behaviour parameters**	Anticoagulant compliance, warfarin knowledge,	Morisky Anticoagulant Compliance Questionnaire [14], Oral Anticoagulation Knowledge (OAK) Test [15]	√				√

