#### Secondary outcome measures

The numbers of INR results indicating excessive under-coagulation or over-anticoagulation (INR < 1.5 or INR > 5.0).Serious adverse clinical events (clinical relevant non-major bleeding, major bleeding, thrombosis or death)Patients’ quality of life.Costs on warfarin management.

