#### Data analyses

We will report continuous variables as means ± SD and categorical variables as proportions. Data will be checked for normal distribution by means of the Kolmogorov–Smirnov’s test. In compliance with the distribution of data, Student’s t-test or Mann–Whitney’s U-test will be used for comparisons between the SMART model group and control group. Chi-square or Fisher’s exact tests will be used to compare between the SMART model group and control group with respect to categorical data. The control of anticoagulation will be assessed by evaluating TTR with the Rosendaal method [18] in each arm. The follow-up assessment data will be analyzed using Generalized Linear Mixed Model and survival analysis. *P* ≤ 0.05 is considered statistically significant. All tests are two tailed. From the perspective of health-care payer, we will conduct a cost-effectiveness analysis to assess the economic impact of the SMART model for warfarin home management. A Markov model, a half-cycle correction and a discount of 5% will be constructed or used to estimate the total costs and quality-adjusted life-years (QALYs) over the 2-year period (the outcomes beyond the observation period will be predicted according to the results obtained in the study). We will collect the direct and indirect costs of each enrolled patient on warfarin, evaluate their quality of life through EQ-5D-3L utility value from data provided by patients, calculate QALYs, and analyze the effects of multiple variables by the Linear Mixed Effects Model. The direct costs include laboratory INR test fees in the control groups (or POCT fees in the SMART model group), outpatient clinic visit fees (or supervision fees in the SMART model group), hospitalization fees and emergency room visit fees. The indirect costs include deducted income due to absence of working, traffic fees and accommodation fees. Because warfarin is very cheap, the medication fee of warfarin is not calculated in each group. The incremental cost effectiveness ratio (ICER) will be calculated according to the total costs and QALYs, and one-way and probabilistic analyses will be performed to verify the stability of the model.

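### A SMART-only dropout rule combined with last observation carried forward can understate clinical event risk in the SMART arm, and no analysis is named as deciding for events

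*Protocol article*

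**What the plan says.** The Study design section promises a comparison of the "incidence of warfarin associated major bleeding and thromboembolic events". Under Secondary outcome measures the event outcome is "Serious adverse clinical events (clinical relevant non-major bleeding, major bleeding, thrombosis or death". No analysis method is tied to it by name.

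The Data analyses section contains two sentences that can apply to it:

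- Chi-square or Fisher's exact tests are to be "used to compare between the SMART model group and control group with respect to categorical data".
- "The follow-up assessment data will be analyzed using Generalized Linear Mixed Model and survival analysis".

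Table 3 (Follow-up visits and data collection) lists "Warfarin dosage, INR, bleeding or thrombosis, other clinical adverse events" among the items collected at months 3, 6, 9 and 12, so events are follow-up data.

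Under Study participants and inclusion criteria, one of the three dropout criteria is that "the patient in the SMART model group does not follow the health-care professionals’ instruction for at least twice". There is no matching criterion for usual care or anticoagulation clinic patients. The same section says of the impact of dropouts, with intention to treat expressly included, that it "will be used by carrying the last observation forward". Events are not exempted.

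**The concern.** For a yes/no event, the last observation of a patient who leaves without an event is no event. Carried forward, it turns a partly observed patient into one counted as event-free for 12 months. If this happened equally in all arms, it would lower every proportion and distort the comparison little. Here one dropout criterion exists in the SMART arm only, so the plan builds in a reason for unequal loss, and the distortion would favour the experimental arm.

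Survival analysis would normally deal with this by censoring. Carry-forward, if applied there as well, replaces censoring with assumed event-free time. Every patient is then followed to an event or to month 12, and the Kaplan-Meier estimate at month 12 equals the crude proportion.

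Safety is one of the questions the Discussion says the trial will answer, with wider use of the model in view. With two methods open for the same outcome, the more favourable one could also be chosen after the data are seen.

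**Working it through.** The protocol gives no event-based sample size or expected 12-month event risk, so there is no figure of its own to reproduce for events. The size of the effect has to be shown over a range.

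**Inputs**

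- Event risk p. Background gives 5.23% for ischaemic stroke and 2.94% for intracranial bleeding in China, without a time unit. Assumption: 12-month risks that can be added, so p = 5.23% + 2.94% = 8.17%.
- SMART-only loss d. Not given. Sample size determination allows 10% dropout overall (31 × 1.10 = 34.1, stated as at least 34). Range used: 5% to 30%.
- Assumptions: equal true hazards in the arms, no loss in controls, and leavers no longer observed.

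**Crude proportion with no event carried forward**

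1. Constant hazard: h = −ln(1 − 0.0817) = 0.0852 per year.
2. Mean observed risk of leavers spread evenly over the year: 1 − (1 − e^(−h))/h = 1 − 0.0817/0.0852 = 0.0414.
3. Observed SMART proportion: (1 − d) × 0.0817 + d × 0.0414.
   - d = 10%: 0.0735 + 0.0041 = 0.0777; ratio to the true risk 0.95.
   - d = 20%: 0.0654 + 0.0083 = 0.0736; ratio 0.90.
4. If all leavers go at month 3, their observed risk is 1 − e^(−0.25h) = 0.0211.

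| SMART-only loss | Ratio, even loss | Ratio, loss at month 3 |
|---|---|---|
| 5% | 0.975 | 0.96 |
| 10% | 0.95 | 0.93 |
| 20% | 0.90 | 0.85 |
| 30% | 0.85 | 0.78 |

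The ratios hardly depend on p: at p = 2.94% or 5.23% the even-loss values are the same to two decimals. Control losses offset part of the effect: with 20% loss in SMART and 5% in controls the risk ratio is 0.92. At 20% against none, a true hazard ratio of about 1.11 would give a crude risk ratio of 1.00.

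**Does censoring cure it?** Take d = 10%, even loss, and let leavers have k times the hazard of the others. The Kaplan-Meier column uses proper censoring at the time of leaving.

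| k | True SMART risk | Crude (ratio) | Kaplan-Meier (ratio) |
|---|---|---|---|
| 1 | 8.17% | 7.77% (0.95) | 8.17% (1.00) |
| 2 | 8.92% | 8.16% (0.915) | 8.56% (0.96) |
| 3 | 9.61% | 8.53% (0.89) | 8.93% (0.93) |

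Censoring removes the bias when leaving is unrelated to risk. It leaves about 4% to 7% relative understatement when the leavers have two to three times the hazard. Only continued event collection closes that gap.

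**The case against.** A reader might infer that the plan sends events to tests that ignore follow-up time. The text does not support that. The chi-square/Fisher sentence names no outcome, survival analysis is planned for follow-up data, and Table 3 makes events follow-up data. Events are also the listed outcome best suited to survival analysis. Which test leads for a secondary outcome would by itself be a detail for the analysis plan. This objection stands, and the point therefore rests on the dropout and carry-forward rules.

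A reader might also infer that follow-up certainly ends at an adherence dropout, or that SMART risk certainly is understated. Neither is stated. The protocol does not say whether event collection stops, and it requires follow-up of all patients to month 12, by telephone or online if needed. Withdrawal for any reason and removal on the researcher's judgement apply in every arm, and Background notes reduced hospital visits in the pandemic, so controls may be lost too. Reporting every two to four weeks may also detect more events in SMART. This stands as a limit on direction and size. Against it, carry-forward is needed only where observation is missing, so the plan evidently expects some to be.

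Finally, the effect is small beside sampling error. With about 28/360 events against 39/480 (both control groups pooled), the standard error of the log risk ratio is √(1/28 − 1/360 + 1/39 − 1/480) = 0.24. The shift at 10% loss, ln 0.95 = −0.05, is about a fifth of that. That is true, but the shift is systematic and can be avoided at almost no cost.

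**Conclusion.** The concern holds in a conditional form. The protocol states an adherence dropout rule for one arm only and a carry-forward rule that does not exempt clinical events. Together they can make SMART event risk look lower than it is, in a proportion test and equally in a survival analysis if carry-forward is applied there.

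For SMART-only loss of 10% to 20% spread evenly over the year, the understatement is about 5% to 10% relative; if loss falls at month 3 it is about 7% to 15%. This assumes that observation stops at dropout, that controls have no offsetting loss, and constant and equal hazards. The loss rates are assumed, and the time unit of the Background event rates is unknown. The protocol does not allow the actual size to be fixed.

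**What to change.** In Study participants and inclusion criteria:

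- Exempt clinical events from last observation carried forward.
- State that event collection through the planned three-monthly telephone or online contacts continues to month 12 after an adherence dropout, unless the patient withdraws consent.

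In Data analyses:

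- State that events are compared by time to first event in all randomised patients, analysed as randomised, censored at last known contact or month 12, and stratified by hospital level.
- State how death is handled: as an event where it is part of the outcome, and as a competing event for bleeding or thrombosis taken alone.
- Describe any chi-square or Fisher comparison of events as descriptive only.

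Confirm that event dates are recorded. The handbook described under Follow-up visits and data collection includes thrombosis and bleeding events but does not mention their dates; if they are not captured, a date field is needed.

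The cost is a few sentences, possibly one data field, and continued use of contacts already planned. Recruitment began in March 2021, so the change should be made soon, and patients already classed as adherence dropouts should be contacted for event status where consent allows.

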	Treatment behavior, quality of life	Self-made questionnaire, EQ-5D-3L Form [16]	√	√	√	√	√
	Anticoagulation satisfaction	Duke Anticoagulation Satisfaction Scale [17]					√
**Economic parameters**	Direct costs (INR test fees, outpatient clinic visit fees, hospitalization or emergency room visit fees if occurs), Indirect costs (deducted income due to absence of working, traffic and accommodation fees)	Face-to-face interview, telephone or online interview	√	√	√	√	√

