Nevertheless, the implementation of warfarin home management faces obstacles in developing countries, including legal and regulatory issues, patients lacking direct and timely access to professional recommendations from health care providers, lack of access to telehealth technology, and limited or no coverage of the POCT device from the government. The current proposed study will take several measurements (the SMART model) to ensure its implementation in China, including using a mobile phone app to assist caregivers managing warfarin more efficiently, establishing medical alliance and multidisciplinary teams to manage patients together to solve the problem of maldistribution of medical care, and using a hierarchical strategy to manage patients to assure their safety. As far as we know, this proposed study will be the biggest multi-center randomized controlled trial to investigate the safety, effectiveness and cost-effectiveness of warfarin home management in China. If our final data demonstrate the SMART model for warfarin home management is cost-effective, this pattern may be applied in more provinces and be expanded to other chronic diseases management.

In the proposed study, we will include hospitals with different qualities of medical service. On the one hand, as the current medical service level in the county hospitals is low, we expect that the differences in TTR, numbers of under-coagulation or over-anticoagulation, and serious adverse clinical events between the SMART model group and the control group may be significantly bigger than the other two levels of hospitals. On the other hand, patients’ quality of life and costs on warfarin management may be improved the most obviously in the big tertiary hospitals, as patients do not have to travel long way to the hospitals.

The biggest limitation of our proposed study is that the nature of the intervention method (the SMART model) excludes patients who are unable to use a POCT device correctly, or fail to report their INR results through a mobile phone based app.

In summary, we have developed a novel model (the SMART model) to investigate the safety, effectiveness and cost-effectiveness of warfarin home management in different areas of Hunan province in China. This model may be particularly useful to manage patients on warfarin during and after the COVID-19 pandemic.

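### The economic analysis claims a health-care payer perspective, but on its plain reading the ICER's total costs include patients' lost income, travel and accommodation

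*Protocol article*

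**What the plan says.** All the main statements stand in one paragraph of the protocol article, under Data analyses.

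- Perspective: "From the perspective of health-care payer, we will conduct a cost-effectiveness analysis".
- Costs gathered: "We will collect the direct and indirect costs of each enrolled patient on warfarin".
- Direct costs: the list opens with "The direct costs include laboratory INR test fees in the control groups (or POCT fees in the SMART model group" and continues with clinic visit or supervision fees, hospitalization fees and emergency room fees.
- Indirect costs: "The indirect costs include deducted income due to absence of working, traffic fees and accommodation fees".
- Exclusion: one item only, the price of warfarin itself.
- Ratio: "The incremental cost effectiveness ratio (ICER) will be calculated according to the total costs and QALYs".

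Table 3, in the section on follow-up visits and data collection, repeats the patient-borne items: "Indirect costs (deducted income due to absence of working, traffic and accommodation fees". They are scheduled at baseline and at months 3, 6, 9 and 12. The article names no second perspective and no second ICER.

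The Discussion expects quality of life and costs to improve most visibly in the big tertiary hospitals because "patients do not have to travel long way to the hospitals".

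**The concern.** The perspective of an economic evaluation decides which costs enter the numerator of the ICER. A health-care payer does not bear a patient's lost wages, fares or lodging. Those items belong to a patient or societal perspective. A plan that names the payer and then sums all collected costs gives a ratio that answers neither question cleanly.

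This could matter to the conclusion because these items are the ones a home-testing programme can be expected to change. The Background says rural patients often travel for hours to reach a tertiary hospital, and it lists travel time and travel cost among the dominant reasons for missed follow-up. SMART's own running items, the POCT and supervision fees, are classed as direct costs. If direct costs rise and patient-borne costs fall, a mixed total can hide a cost increase to the payer. The Discussion says the model may be applied in more provinces if it proves cost-effective, so readers would rely on the label attached to the ICER.

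**Working it through.** **Step 1: is there a figure to reproduce?** No. The article gives no ICER, cost difference or QALY difference. Its only unit costs, in the Background, are about $3,000 for thrombosis and $4,500 for intracranial hemorrhage. Both are in-hospital direct costs and say nothing about the size of indirect costs.

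**Step 2: what does total costs cover?** The phrase occurs twice in the Data analyses paragraph: in the sentence on the Markov model (two-year horizon, 5% discount) and in the ICER sentence. Between the two, the text says that both direct and indirect costs are collected, defines each, and names one excluded item, the warfarin drug cost. Neither occurrence is limited to direct costs or to payer costs. The article never writes that total equals direct plus indirect, but that is the natural reading of the order.

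**Step 3: effect on the ratio.** Let ΔD, ΔI and ΔQ be the differences, SMART minus control, in direct costs, indirect costs and QALYs.

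- ICER on total costs = (ΔD + ΔI)/ΔQ
- ICER on direct costs = ΔD/ΔQ
- Shift from including indirect costs = ΔI/ΔQ

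With a QALY gain, the shift has the sign of ΔI. It is negative, in SMART's favour, only if SMART lowers patients' indirect costs.

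**Step 4: illustration.** Every input here is assumed, in unnamed currency units.

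| ΔI | Shift at ΔQ = 0.01 | Shift at ΔQ = 0.03 |
|---|---|---|
| -300 | -300/0.01 = -30,000 | -300/0.03 = -10,000 |
| -100 | -100/0.01 = -10,000 | -100/0.03 = -3,333 |
| 0 | 0 | 0 |
| +100 | +100/0.01 = +10,000 | +100/0.03 = +3,333 |

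A case in which the label changes the message: ΔD = +300, ΔI = -300, ΔQ = 0.03. On direct costs the ICER is 300/0.03 = 10,000 per QALY. On total costs it is (300 - 300)/0.03 = 0, and the programme looks cost-neutral.

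**Step 5: are the listed direct costs all payer costs?** Not necessarily. The Discussion names limited or absent government coverage of the POCT device as an obstacle in developing countries. If patients pay part of the direct costs, with between-arm difference ΔU, the payer ICER is (ΔD - ΔU)/ΔQ. The mixed ratio then differs from it by (ΔI + ΔU)/ΔQ. If SMART patients pay more out of pocket for testing, ΔU is positive and works against the expected saving in ΔI.

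**The case against.** The strongest reply is that the link is inferred. Total costs first appears directly after the payer sentence and before indirect costs are mentioned, so it could mean cumulative modelled costs within the payer perspective. Collecting indirect costs does not by itself put them in the ICER, and they have another possible use: costs of warfarin management are a separate secondary outcome. This reading is possible but less natural. The indirect items are defined inside the description of the economic analysis, ahead of the ICER sentence, and only the drug cost is set aside.

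A second reply is that a condensed article leaves itemised costing to the full plan. That would cover missing detail. Here the article states both the perspective and the cost set, and the two do not fit.

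Stronger readings are tempting, but the documents do not support them:

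- A reader might infer that the ICER is certain to be biased towards SMART. The text gives an expectation of less travel, not a result. SMART patients labelled dangerous are advised to go to hospital, and follow-ups in any arm may be clinic visits.
- A reader might infer that avoided travel is SMART's main saving. The article also expects fewer complications, which would be direct-cost savings, and it lists POCT and supervision fees as counterparts of laboratory and clinic fees rather than as pure additions.
- A reader might multiply trips avoided by cost per trip to size the effect. The article gives neither number.
- A reader might infer that a coverage decision is planned. The Discussion speaks of wider application and mentions coverage as an obstacle and as United States history.

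**Conclusion.** The point holds as a mismatch between the declared perspective and the cost set of the ICER, on the plain reading of the Data analyses paragraph. It is more than missing detail, because the choice changes what the ratio means. The amount at issue is ΔI/ΔQ. The protocol's expectation of less travel suggests that this favours SMART, but neither direction nor size can be established from the article. The 3,333 to 30,000 per QALY range rests wholly on assumed savings of 100 to 300 units and assumed gains of 0.01 to 0.03 QALYs. Because it is uncertain who pays for the POCT device, direct costs cannot simply be taken as payer costs either. The primary TTR outcome is unaffected. The matter should be settled before cost data are analysed, so that the perspective is not chosen with results in view.

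**What to change.** State in Data analyses that the payer base-case ICER includes only items the payer bears, drawn from the listed direct costs, and excludes lost income, travel and accommodation. Specify who pays the POCT fees and the supervision fees, and treat each accordingly. Report a second, separately labelled societal ICER that adds the patient-borne items. Alternatively, relabel the whole analysis as societal and make no payer claim.

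No new data collection is planned for this, since Table 3 already schedules every cost item. The cost is a short text change, one additional analysis under the first option, and a payer ICER that may look less favourable than the mixed one.

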## Background

In line with the increasing aging population, the incidence and prevalence of atrial fibrillation (AF) and other thromboembolic diseases have dramatically increased and become a significant health problem worldwide [1]. Patients with these conditions should take long-term or lifelong anticoagulant drugs to prevent or treat thrombosis. It’s estimated that at least 0.6% of people in China need anticoagulation therapy [2, 3].

Although the new oral anticoagulants (NOACs) have been used as alternatives to warfarin due to good safety and less monitoring, warfarin remains the first line anticoagulant in certain conditions, including mechanical heart valve replacement, severe mitral stenosis, renal failure and etc. In addition, anticoagulant choice is impacted by patients’ individual preference, insurance allowance and personal economic situation. Therefore, warfarin will continue to be widely used across the world.

Warfarin treatment is cheap and effective, but requires frequent monitoring to adjust dosage under professional guidance. In China, patients and families from rural locations often need to travel several hours to tertiary hospitals in big cities to get quality warfarin monitoring and dosing, resulting in poor compliance, limited monitoring frequency, high incidence of warfarin related complications and increased costs. During the COVID-19 pandemic, many patients with chronic diseases, including patients on warfarin, have reduced their visits to hospitals due to the social distancing policy and shortage of medical resources.

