In China, the percentage of time in therapeutic range (TTR, a tool of measuring warfarin treatment effects) was less than 40%, which was significantly lower than that of 62% in western countries [4]. Clinical observation studies found that warfarin associated ischemic stroke and intracranial bleeding were respectively 5.23 and 2.94% in patients from China, significantly higher than patients from the rest of the world (2.94 and 0.63%, respectively) [5]. In warfarin-treated patients in China, the median in-hospital direct cost per patient was about $3, 000 for thrombosis and $4, 500 for intracranial hemorrhage [6]. These data suggest that warfarin management in China needs further improvement. An investigation study launched by the PI using the Andersen’s Health Services Utilization Behavioral Model in 469 patients on warfarin indicated that long time and high cost for travel, low family income, low quality of warfarin monitoring and dosing in local hospitals were dominant reasons for missing follow-ups (data not published yet).

Anticoagulation clinics (AC) have been proved safer and more effective than usual care in warfarin management [7, 8], but there are only about 50 ACs located in big cities of China (mainly run in a physician-pharmacist cooperative AC pattern) at present. The number of ACs is too low, and it is not easy to open more ACs due to limitation of health care professionals and longtime education.

Point-of-care testing (POCT) device designed for measuring INR by patients or their families was first developed in 1980s in America [9] and then widely used in many developed countries. Compared to traditional laboratory INR test in outpatient clinics, POCT has great advantages in convenient home testing and fast result reporting. Soon patient self-testing (PST) for warfarin home management by using POCT devices and telehealth has been rapidly applied in developed countries. Although the PST model of warfarin management has demonstrated improvement of clinical outcomes compared to usual care clinics and anticoagulation clinics [10], it is rarely applied in developing countries, including China.

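### The cost-effectiveness analysis takes the payer's perspective, but patient interview is the only stated source of the Table 3 fees, with no payer/patient split, so they cannot be shown to be payer costs

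*Protocol article*

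**What the plan says.** The Data analyses section sets the viewpoint: "From the perspective of health-care payer, we will conduct a cost-effectiveness analysis". It then lists the cost items. For direct costs it begins: "The direct costs include laboratory INR test fees in the control groups (or POCT fees in the SMART model group"; clinic visit fees (supervision fees in the SMART arm), hospitalization fees and emergency room fees follow. Indirect costs are lost income, travel and accommodation. The ICER is formed from total costs and QALYs.

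The section Follow-up visits and data collection says where the data come from. Of each follow-up it says that "patients are required to provide the information of warfarin dosage and INR results", and the same list ends with "quality of life as measured by the health index scale (EQ-5D-3L) [16], and the related treatment costs". The list also includes the number of outpatient visits and inpatient treatments due to warfarin.

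In Table 3 the economic row reads "Direct costs (INR test fees, outpatient clinic visit fees, hospitalization or emergency room visit fees if occurs" and goes on to the indirect items. Its measurement method is "Face-to-face interview, telephone or online interview". No bill, claim, tariff or hospital record is named for any cost item. Supervision fees do not appear in Table 3.

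**The concern.** A payer analysis needs the amount the payer paid. A patient interview can yield one of two figures: what the patient paid personally, or the full bill. The first is the patient's share and the second is the payer's and patient's shares together. Neither equals the payer's cost unless the split is known, and the split is not among the stated cost items.

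Two features make this more than a labelling matter. First, amounts are recalled over three-month intervals, and the people with the largest bills are the most likely to be lost as informants. Death, major bleeding and thrombosis are listed secondary outcomes, and a patient who dies or is disabled may not be able to report the admission. Second, the error need not be equal in the two arms. The Discussion remarks, about developing countries in general, that government coverage of the testing device is limited or absent. If that held here while admissions were partly reimbursed, out-of-pocket reports would count the device fees in full and avoided admissions only in part.

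Cost is a secondary outcome, and the Discussion ties wider roll-out to a favourable cost-effectiveness result. The Markov model also runs to 2 years on 12 months of observation, so a mis-valued first year would carry forward if the observed costs feed the prediction.

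**Working it through.** The article states no cost total, reimbursement rate or ICER, so there is no plan figure to reproduce. The check has two parts.

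**1. Perspective against source**

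| Element | Where | Content |
|---|---|---|
| Perspective | Data analyses | Health-care payer |
| Source of listed fees | Follow-up section and Table 3 | Patient report by interview |
| Gross, reimbursed or out-of-pocket | Nowhere | Items are called fees only |
| Payer/patient split | Nowhere | Not a listed item |
| Supervision fees | Data analyses only | No source stated |
| Lost income, travel, accommodation | Table 3 and Data analyses | Collected, and on the natural reading part of the total costs in the ICER, although a payer does not bear them |

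**2. How much the definition of a fee could matter (illustration)**

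Inputs from the documents:
- Ischemic stroke on warfarin in China, 5.23% (Background). No time base is given; it is treated here as a 12-month risk, which is an assumption.
- In-hospital cost (Background): "the median in-hospital direct cost per patient was about $3, 000 for thrombosis and $4, 500 for intracranial hemorrhage". The $3,000 thrombosis figure is applied to the stroke rate. It is a median, so the product is not a true expected cost.
- A 50% reduction in thromboembolic events with home management (Discussion).

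Input not in the documents: the patient's share *s* of the bill, varied over 0.3, 0.5 and 0.7.

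Gross saving per patient = 0.0523 × 3,000 × 0.5 = 156.9 × 0.5 = $78.45.

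True payer saving = 78.45 × (1 − *s*). Recorded saving = 78.45 × *s* if patients report out-of-pocket amounts, or 78.45 if they report the full bill. The relative errors are *s*/(1 − *s*) − 1 and 1/(1 − *s*) − 1.

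| *s* (assumed) | Payer-paid saving | Out-of-pocket report | Error | Gross report | Error |
|---|---|---|---|---|---|
| 0.3 | $54.92 | $23.54 | −57% | $78.45 | +43% |
| 0.5 | $39.23 | $39.23 | 0% | $78.45 | +100% |
| 0.7 | $23.54 | $54.92 | +133% | $78.45 | +233% |

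The relative errors depend only on *s* and on what is reported. The weak event rate and median cost affect the dollar figures but not the percentages. With out-of-pocket reports the sign of the error changes at *s* = 0.5.

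**The case against.** The strongest reply is that the article never says patients report only what they paid. It says fees, and an interview can record a billed total. Visit and admission counts are collected as well. Multiplied by unit costs, they would value care in the Markov model without using recalled payments. Bill verification, the unit-cost source and the gross or net definition are details that a journal article commonly leaves to a fuller document.

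Much of this stands. A reader might infer that the payer's share is not collected and that the direct costs in the ICER are therefore wrong. The document does not support that: it shows costs that cannot be demonstrated to be payer costs, not costs shown to be in error. A reader might also infer that the recorded saving is 50–70% too small. That compares out-of-pocket reports at shares of 50% and 30% with the gross saving. Against the payer-paid saving, the shortfall is 57% at a 30% share, zero at 50%, and reversed above that. Nor is it shown that the sign of incremental cost would change. No SMART cost figure is given, and nothing says that SMART's own fees are known in full. The Background's mention of "insurance allowance and personal economic situation" concerns the choice of anticoagulant, so it is weak evidence on reimbursement of tests or admissions.

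The reply does not remove the mismatch. Table 3 has a column for the measurement method and fills it with interview, so the source is stated rather than omitted. A gross bill is no more a payer cost than an out-of-pocket payment is, unless payer is taken to mean all payers together, which the article does not say. An analysis plan can choose a valuation, but it cannot recover a split that was never recorded.

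**Conclusion.** The concern holds in this limited form: the stated source of the Table 3 fees does not fit the stated perspective. As written, the recorded direct costs cannot be shown to be payer costs, and the source of the supervision fees is not given. Including lost income, travel and accommodation in the total costs is a second mismatch with the same perspective and belongs in the same correction.

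Neither the size nor the direction of the error in the ICER can be determined from the document. At an assumed 30% patient share, the saving on admissions would be 57% too small with out-of-pocket reports and 43% too large with gross reports; at 50%, out-of-pocket reports give no error. These figures rest on an assumed share and show only that the answer depends on a definition the article does not fix. The primary outcome, TTR, is not affected.

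**What to change.** 1. Take INR, outpatient, emergency and admission charges for care at the nine participating hospitals from their billing records, split into payer-paid and patient-paid. Where no split is available, value the visit and admission counts already collected at payer unit costs.
2. Keep the interview for care received elsewhere and for travel and lost income.
3. State the source of the SMART supervision fees and add them to Table 3.
4. Build the payer ICER from payer-paid costs only, leaving out lost income, travel and accommodation. Alternatively, restate the perspective so that it matches the costs actually collected.
5. Correct the measurement-method entry for economic parameters in Table 3.

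The cost is some data-extraction work at each hospital. It assumes that the hospitals hold billing data in usable form, which the article does not say. Recruitment began in March 2021 and the Data monitoring section requires ethics approval for important procedure changes, so an amendment may be needed. Restating the perspective avoids the extraction but gives up the payer result.
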